As part of the cost-utility analysis (Objective 2) and hybrid mathematical model (Objective 3), the efficiency of the ED models of care will be assessed using an incremental cost-effectiveness ratio (ICER). The resulting ICER will be reported in terms of incremental cost per quality-adjusted life years (QALY) gained, between the models of care. The follow-up costs of each participant recorded via the self-administered follow-up questionnaires completed at 1 and 3 months during the pilot pragmatic RCT will be added to the distribution of ED visit costs for each individual obtained under Objective 1. Once all costs have been added, an average will be calculated to obtain an average cost per participant at 3 months, for each model of care (Objective 2 & 3 –decision tree). The questionnaires provided data on resources used by each participant during follow-up such as ED re-visits for the same condition, number of consultations with other health professionals in the public and private sector, imaging tests used, etc. The costs of all resources used in the public healthcare system will be drawn from public cost repositories data from the *Régie de l’assurance-maladie du Québec* (RAMQ) (costs related to the emergency physician and other physicians consulted, drugs, laboratory analysis, imaging tests) [47]. Hourly rates for the primary contact physiotherapist and other health professionals consulted (e.g., massage therapist, chiropractor, osteopath) will be derived from a search of the grey literature and will be based on rates in effect within the private healthcare system, since the majority of these professionals work within this system [47]. Costs related to the use of technical aids (e.g., cane, crutches, walker) will also come from a grey literature search. It should be noted that the salary data available from human resources for all healthcare professionals (physicians and allied health professionals) considered will not allow for variability in hourly costs. The only source of variability considered for the purpose of these analyses will be that related to the time required for ED processes. Utility scores were obtained at the initial visit [48] and at 1 and 3 months using the EQ-5D-5L, a generic standardized questionnaire designed to measure health status in an economic and clinical evaluation [49]. The EQ-5D-5L has been found to be reliable, valid, and sensitive to change [50, 51]. The difference in utility scores between the 3-month follow-up and baseline will be calculated for each participant using area-under-the-curve analyses. Once the difference in utility scores will be calculated for each participant, the differences will be averaged to obtain the average gain or loss in utility scores per ED care model. The mean gain or loss in utility scores will then be transformed into QALYs. The efficiency values and the costs from 3 to 24 months required to run the Markov model (Objective 3) for the three models of care will be taken from the literature.

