
### Data analysis and interpretation of results

As part of Objective 1, a mapping of the care pathways encountered will be completed for each type of MSKD encountered in our study population (i.e., low back pain, neck pain, upper limb, lower limb) (Fig 1). The unit cost of each of the resources, consumables and indirect costs required in each process of care of the care pathway will be calculated and multiplied by the duration of each process to obtain the cost related to each process of care present in the care pathway. The costs associated with each process will be summed to obtain the total cost of the ED care pathway specific to each MSKD and each model of care (i.e., emergency physician or primary contact physiotherapist and emergency physician management). A generalized linear model with a Gamma distribution and log link will be used to test whether there is a significant difference in the costs of managing equivalent MSKDs between the two models of care [52, 53].

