**Fig 3 pone.0277369.g004:**
[figure not shown]
Projected Markov model covering the period from three to 24 months post initial ED visit.

Both the cost-utility analysis (Objective 2) and the hybrid mathematical model (Objective 3) will be conducted from a Health system and a Societal perspective. Results obtained via the EQ-5D-5L at 1 and 3 months (Objective 2 & 3 –decision tree) will be converted to utility scores using the Canadian conversion algorithm developed by Xie et al. [54]. As the 3-month retention rate for the pilot pragmatic trial was 80% [29], some participants’ data are missing (service and resource use, costs, utility scores). Missing data will be imputed using the Missing not at random (MNAR) multiple imputation method [55]. Patient characteristics believed to have influenced loss to follow-up at 1 and 3 months (e.g., socioeconomic status; level of pain and level of catastrophizing at the ED visit) will be examined to identify if they are indeed predictors of loss to follow-up. Characteristics shown to influence follow-up will be used within multiple imputations and within sensitivity analyses regarding these variables. Uncertainty in cost and effectiveness measures for the cost-utility analysis (Objective 2) will be obtained using non-parametric bootstrap resampling with replacement. Uncertainty in the hybrid model parameters (probabilities, costs, and efficiency) (Objective 3) will be obtained via a probabilistic sensitivity analysis performed using a Monte Carlo simulation. Three scenarios will be considered in the probabilistic sensitivity analyses. The first will assume that all participants with missing follow-up data in the control group will have utility scores at 3 months corresponding to those of the 95th percentile, while all those missing in the intervention group will have scores corresponding to those of the 5th percentile. For the second scenario, we will re-analyze all parameters included in the model, excluding outliers. Finally, in the third and last scenario, the different states of the Markov Model will be based not on the level of pain, but on the level of interference of pain on daily activities. Both uncertainties will be represented visually using a cost-effectiveness diagram, cost-effectiveness acceptability curve, and cost-effectiveness acceptability frontier [35]. As there are significant differences between men and women in the strategies used to cope with pain, and the use of health system services and resources during a painful episode (e.g., [56, 57]), subgroup analyses of men and women will be performed for both objectives (p < .05). Subgroup analyses will also be performed according to MSKD category (spine, upper extremity, and lower extremity) for both objectives (p < .05). All the statistical analyses carried out as part of this project and their detailed reporting in scientific publications will adhere to the CHEERS 2022 standard [58].

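### The p < .05 attached to the sex and MSKD-category subgroup analyses of Objectives 2 and 3 has no defined test behind it and does not suit an ICER or a simulation model

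*Protocol article*

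**What the plan says.** The subgroup plan is in the last paragraph of the Data analysis and interpretation of results section, after Fig 3. That paragraph opens by naming its two objectives: "Both the cost-utility analysis (Objective 2) and the hybrid mathematical model (Objective 3) will be conducted from a Health system and a Societal perspective". It then plans two sets of subgroup analyses with a significance level: "subgroup analyses of men and women will be performed for both objectives (p < .05"), and "Subgroup analyses will also be performed according to MSKD category (spine, upper extremity, and lower extremity) for both objectives (p < .05"). In this context the two objectives are Objectives 2 and 3.

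For those objectives the Study outcomes section says that "the efficiency of the ED models of care will be assessed using an incremental cost-effectiveness ratio (ICER"). Uncertainty for Objective 2 "will be obtained using non-parametric bootstrap resampling with replacement"; for Objective 3 it "will be obtained via a probabilistic sensitivity analysis performed using a Monte Carlo simulation". The presentation is graphical: "Both uncertainties will be represented visually using a cost-effectiveness diagram, cost-effectiveness acceptability curve, and cost-effectiveness acceptability frontier".

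The one significance test that the article names is the Gamma GLM with log link. It belongs to Objective 1, where it is to "test whether there is a significant difference in the costs of managing equivalent MSKDs between the two models of care".

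**The concern.** A significance level needs a quantity, a null hypothesis and a test. Here the level is given and the other three are not, and the analyses around it do not supply them. An ICER is a poor candidate for a test: it is undefined when the QALY difference is zero, unstable near zero, and the same value can lie in opposite quadrants of the cost-effectiveness plane.

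Objective 3 raises a further difficulty. The Data collection section says that the physiotherapist-alone model was not observed in the RCT and takes all its parameters from the literature. The Study outcomes section takes the costs and effectiveness from 3 to 24 months from the literature for all three models. Sampling evidence from 78 patients is therefore only part of what the simulation carries.

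At stake is a conclusion that one model is efficient in women but not in men, or for the spine but not the limbs, resting on one subgroup crossing .05 and another not crossing it. That pattern does not show that the effect differs, and at this sample size it will often arise by chance.

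**Working it through.** The article gives no power, SD or error rate for subgroups, so there is no figure of its own to reproduce.

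**Inputs from the article.** n = 78 in two arms; 3-month retention 80%; sex with 2 levels; MSKD category with 3 levels; 2 objectives; 2 perspectives; threshold .05.

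**Assumptions not in the article.** 1:1 arms, equal split by sex, equal thirds by region, approximately normal outcomes, two-sided tests, and the effect sizes and correlations below.

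**1. Does any planned method yield the p-value?** Objective 2: bootstrap replicates of cost and effect. Objective 3: Monte Carlo draws. Display: diagram, acceptability curve and frontier. None is described as a test, and the Gamma GLM is tied to Objective 1 costs. So the threshold has no stated source.

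**2. A p-value across draws (Objective 3).** For N draws with mean difference m and SD s, the test statistic is m/(s/√N) = (m/s)·√N. Four times as many draws doubles it, with no new patient data.

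**3. Cell sizes.** Completers: 78 × 0.80 = 62.4, or 31.2 per arm. Per sex per arm: 31.2/2 = 15.6. Per region per arm: 31.2/3 = 10.4.

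**4. Detectable difference within a subgroup,** 80% power: (1.96 + 0.84)·√(2/n) SD.
- Sex: n = 15.6 gives 1.00 SD.
- Region: n = 10.4 gives 1.23 SD.

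**5. Spurious disagreement.** Suppose the true effect is the same in each of g subgroups, each reaching p < .05 with probability P. The chance that they do not all agree is 1 − P^g − (1 − P)^g. At 0.5 SD:
- Sex: P = 0.287, g = 2, giving 1 − 0.287² − 0.713² = 0.41.
- Region: P = 0.207, g = 3, giving 1 − 0.207³ − 0.793³ = 0.49.

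Other effect sizes:

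| True effect, all subgroups | Sex | Region |
|---|---|---|
| 0 | 10% | 14% |
| 0.3 SD | 23% | 28% |
| 0.5 SD | 41% | 49% |
| 0.8 SD | 48% | 74% |

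Counting all 78 patients (19.5 and 13 per cell; P = 0.345 and 0.247) does not help at 0.5 SD: 1 − 0.345² − 0.655² = 0.45 and 1 − 0.247³ − 0.753³ = 0.56.

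**6. At least one false positive when no effect exists.** Independent within-subgroup tests, 1 − 0.95^k:
- k = 5 (2 sexes + 3 regions): 22.6%.
- k = 10 (× 2 objectives): 40.1%.
- k = 20 (× 2 perspectives): 64.2%.

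The tests are not independent, so all 20 were also simulated under the null (62 completers, 3000 runs). The result was 21% if all four outcomes coincide, 37% with correlations of 0.9 between perspectives and 0.9 between objectives, 50% with 0.8 and 0.5, and 61% with zero correlation.

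**7. After the change.** One interaction test per factor on one quantity: 1 − 0.95² = 9.75% (simulated 9.9%), against 22.6% (simulated 20.9%) for five within-subgroup tests. The sex interaction has SE √(4/15.6) = 0.506 SD. It needs 2.80 × 0.506 = 1.42 SD for 80% power and has about 17% power at 0.5 SD. Even done properly, these analyses can only be exploratory.

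**The case against.** The strongest reply is that this is a condensed article and the form of the test is usual content for an analysis plan that is not shown. The wording would fit one arm-by-factor test for each of two factors as well as five within-subgroup tests. With one test per factor over two objectives, the independent-test figure is 1 − 0.95⁴ = 18.5%. The article also gives a rationale for the sex subgroup, already plans acceptability curves, and commits to CHEERS 2022. Its Discussion asks for cautious interpretation and concedes that the sample may limit how much subgroup analysis is done.

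Much of this stands. Four stronger readings are tempting, and the article does not support them:
- **That interaction tests are ruled out.** The text is silent; it does not exclude them. Nor does it state a rule for declaring a subgroup difference.
- **That chance findings are likely.** The 40% and 64% figures need independent within-subgroup tests. Societal costs contain health-system costs, and the decision tree reuses the 3-month trial data of Objective 2, so the tests are correlated.
- **That Objective 3 can always be pushed below .05.** This holds only if draws are treated as a sample and their mean is tested, which the article does not say. The share of draws favouring a model converges as draws increase.
- **That Objective 1 lacks its main contrast.** The objective asks for costs by type of MSKD under the two models, and the named GLM compares costs for equivalent MSKDs. The two match.

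The reply does not remove the misfit. The threshold is written into the article for an outcome and methods that do not generate it. The general caution neither withdraws it nor labels the subgroups exploratory.

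**Conclusion.** The point holds in limited form. The article fixes a significance level for ICER subgroup analyses without saying what is tested, and its stated uncertainty methods do not produce such a p-value. The misfit is clearest in Objective 3, where the inputs come partly from the literature.

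The consequence is conditional. If the threshold is applied subgroup by subgroup, there is a substantial risk of apparent heterogeneity where none exists: about 41% for sex and 49% for region at a common 0.5 SD effect, and roughly 21% to 64% for at least one false positive under no effect. The disagreement figures rest on the assumed balance, normality and effect size. The false-positive range depends on how many tests are run and how strongly they correlate. A single interaction test per factor would carry much less risk, but the article does not commit to one. This should be corrected; it does not undermine the main analyses.

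**What to change.** Delete the p < .05 from both subgroup sentences.

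- **Objective 2:** estimate the arm-by-subgroup interaction on net monetary benefit at stated willingness-to-pay thresholds, or on incremental cost and incremental QALYs. Use one model per factor (sex, MSKD category), report 95% intervals, and label the results exploratory. Net monetary benefit is one sound choice, not the only one; the need is to name the quantity.
- **Objective 3:** present acceptability curves by subgroup, with no hypothesis tests.

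No new data are needed. The cost is a change of wording and minor programming, and fewer positive subgroup statements can be made.

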
### Ethical considerations and data management

This project and all of its components (conduct of the RCT, three-month participants’ follow-up, access to nominative and administrative databases) were approved by the CHU de Québec–UL’s Ethical review board (approval number: MP-20-2019-4307). The randomized clinical trial was also registered with the US National Institutes of Health (#NCT04009369). Each participant signed a written consent form prior to participation. All data collected will be kept in a secure repository and destroyed thereafter. All members of the research team signed a confidentiality agreement.

## Discussion

The overall aim of this project is to evaluate the costs of different models of care for the management of MSKDs in the ED. This will be achieved through three specific objectives: 1) to compare the average costs of an ED consultation and care for various MSKDs; 2) to evaluate the incremental cost-effectiveness ratio (ICER) of two ED models of care for the management of MSKDs over a three-month period post-initial ED visit; and 3) to estimate the ICER between ED models of care for the management of MSKDs over a two-year period.

Until now, there has been no formal economic evaluation of the inclusion of a primary contact physiotherapist in the ED compared with usual practice (emergency physician). The only studies that have been done on the subject have assumed that the effectiveness of the primary contact physiotherapist’s management in the ED is equivalent to that of usual care by the emergency physician. However, several studies have reported that primary contact physiotherapist management can reduce the use of services and resources during the ED stay [8, 26–29, 59]. This research project will fill an important need in the literature by providing an in-depth analysis of the costs and efficiency of the considered models of care. Indeed, this project will help identify the most efficient ED model of care. These models of care also have the potential to improve the quality of services offered to people with MSKDs, their clinical evolution and their quality of life. The increased use of various health professionals in the management of patients in contexts such as the ED can pave the way for the development of new avenues of practice and potentially more efficient organization of services that will benefit the population.

This study is associated with some potential limitations. First of all, the data needed to carry out Objectives 1 and 2 will partly be based on results from a pilot pragmatic RCT. Therefore, the results obtained should be interpreted with caution. The small sample size (n = 78) could possibly limit analyses on the number of plausible branches in the final decision tree as well as the amount of subgroup analysis that will be performed. In addition, although high, the retention rate at the 3-month follow-up of the RCT was 80% [29], which implies that some data related to the use of services and resources, costs and health-related quality of life will be missing. However, this limitation will be mitigated using multiple imputation methods [55]. Sensitivity analyses will also be performed to assess the robustness of the results obtained. Finally, it may be difficult to obtain some of the data on medium- and long-term costs and measures of effectiveness for the ED models of care studied in Objective 3 from the scientific literature. Nevertheless, estimates can be obtained by soliciting the opinions of experts in the fields of MSKD management and emergency medicine, as this method is regularly used in modeling [35].

As for knowledge translation, following the project, formal presentations will be made to all key stakeholders at the CHU (emergency physicians, physiotherapists, nurses, orderlies, patient representatives and administrators) on site or remotely to present the results of the study and discuss lessons learned and future avenues. The results of this project will also be shared with provincial stakeholders (professional associations, patient associations and governments). They will also be disseminated at national and international scientific conferences on economics, health services organization and emergency services. Four manuscripts will be published in peer-reviewed journals. If successful, this project will help guide economic evaluations for a large-scale, multi-center trial aiming to improve the management of people presenting with a MKSD in the ED.
